#### ELISPOT analysis

IFN-γ-ELISPOT assay will be performed using a commercial kit (Tema Ricerca, Bologna, Italy) according to the manufacturer’s instructions. Total PBMCs (10^5^ cells/well) will be used as responding cells and stimulated with 1 μg/mL of peptide covering the entire set of tumor antigens known to be expressed in melanoma (tyrosinase, MART1, MAGEA3, MAGEA1, gp100, NY-ESO, SOX2 and survivin; JPT GmbH, Germany). Plates will be evaluated by a computer-assisted ELISPOT reader (Eli.Expert, A.EL.VIS, Hannover, Germany). The patients’ DTH scores will also be evaluated in combination with IFN-γ-ELISPOT analysis of tumor antigen-specific circulating effectors in the different treatment arms with the same time schedule. In particular, if no significant difference across the treatment arms is found for DTH testing, the distribution of the fold increase (*i.e*. the post-vaccine: pre-vaccine ratio values) in Spot Forming Cells (SFC)/100,000 total PBMC recorded after at least four vaccine doses compared to pre-vaccine values, obtained by ELISPOT analysis and after subtraction of SFC observed in non-stimulated PBMC, will be evaluated using the Student’s t-test across the different treatment arms. If differences are found to be statistically significant (significance level 0.05), the specific primary objective will be considered fulfilled.

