#### Immunologic objective

The immunologic efficacy of the different external immunostimulant conditions used in combination with the autologous tumor lysate-loaded DC vaccine will be assessed by DTH development against KLH and tumor homogenate and also by IFN-γ-ELISPOT analysis of circulating effectors specific for tumor antigens known to be expressed in melanoma, as described in the “Immunologic endpoint assessment” section.

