### Immunologic endpoint assessment

#### Immunologic efficacy

Immunologic efficacy, *i.e*. the ability of the different treatments to efficiently induce an anti-tumor immune response, will be measured by the DTH test against ATL and KLH after at least four vaccine induction doses. DTH testing will be performed in all patients on day −1 (*pre*-*treatment DTH*, which showed no reactivity in the vast majority of patients evaluated in our previous studies), and one day before the 5th, 8th, 11th and 14th vaccine dose (*post*-*treatment DTH*). Scalar doses (100, 50, 20, 10 and 5 μg) of autologous tumor lysate and KLH (pulsed into DC together with tumor lysate as an adjuvant) will be used. The diameter of the induration/erythema observed after 24 hours will be recorded according to the following scale: 0–5 mm grade 1, 6–10 mm grade 2, 11–20 mm grade 3, >21 mm grade 4. As DTH reactivity to lower concentrations of the antigen (s) is closely related to more intense antigen-specific immune response, the score results will be normalized against the concentration itself and transformed into a 0–80 scale for analysis purposes.

The best result obtained for each patient at any of the post-treatment DTHs, either for ATL or KLH, will be taken into account for data analysis (best normalized score). The best normalized score distributions across the different treatment arms will be evaluated according to non-parametric tests and, if the differences are found to be statistically significant, the specific primary objective will be considered fulfilled.

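### ELISPOT gives the primary immunologic objective a second, unadjusted 0.05 chance after DTH fails, by a two-group test applied to four arms with no contrast named

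*Protocol article*

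**What the plan says.** Under Primary objectives, Immunologic objective, the protocol article says efficacy is assessed by DTH "and also by IFN-γ-ELISPOT analysis of circulating effectors specific for tumor antigens". Both assays therefore belong to the primary immunologic objective.

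Immunologic efficacy gives the DTH analysis: "The best normalized score distributions across the different treatment arms will be evaluated according to non-parametric tests". The same sentence goes on to set the success rule for DTH: "if the differences are found to be statistically significant, the specific primary objective will be considered fulfilled". No significance level and no named test are given.

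ELISPOT analysis gives the fallback. It starts "if no significant difference across the treatment arms is found for DTH testing, the distribution of the fold increase". The variable is "the post-vaccine: pre-vaccine ratio values" of spot-forming cells, "after subtraction of SFC observed in non-stimulated PBMC". The test is Student's "t-test across the different treatment arms". The rule ends: "If differences are found to be statistically significant (significance level 0.05), the specific primary objective will be considered fulfilled".

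The three sections on vaccine yield, DC potency and TEM-8 expression also use Student's t-test, but each names a two-group contrast, IFN-α against no IFN-α. The ELISPOT section names none.

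**The concern.** Three features of the ELISPOT rule need attention.

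1. **Two chances at one objective.** The second test is opened by failure of the first and is run at an unreduced 0.05. This is the reverse of gatekeeping, where a later test is allowed only after an earlier success.
2. **The test does not fit the comparison.** Student's t-test compares two groups and there are four arms. Either one contrast must be picked or several t-tests must be run, and the text settles neither. On a primary objective, that choice could be made after the data are seen.
3. **The ratio can be undefined.** After background subtraction the pre-vaccine count can be zero or negative, and no rule is given for such patients. With about six patients per arm, losing or distorting one or two values matters.

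At stake is the statement that the primary immunologic objective was met, which is the trial's proof-of-principle claim.

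**Working it through.** **Inputs.** Four arms with at least six patients each (Leukapheresis and vaccine manufacturing). ELISPOT level 0.05 (ELISPOT analysis). Assumed, because the article does not give them: DTH is a single four-arm rank test at 0.05, tests are two-sided, and no arm differs on either endpoint.

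**The plan's own figure.** The 0.05 is a per-test level, and it reproduces: on normal data a single ELISPOT test rejects in 4.9-5.0% of simulated null trials. The protocol gives no overall figure for the DTH-then-ELISPOT sequence.

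**Overall error.** With independent endpoints, and a_D and a_E the false-positive rates of the DTH and ELISPOT stages,

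P(falsely fulfilled) = 1 − (1 − a_D)(1 − a_E).

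For one test each at 0.05: 1 − 0.95 × 0.95 = 9.75%. Whatever the correlation, it cannot exceed 0.05 + 0.05 = 10%.

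a_E depends on how the t-test wording is read. The values below come from simulated null trials (4 arms × 6); the log-normal ratios have log-SD 1.

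| Reading of the ELISPOT test | a_E normal | Overall normal | a_E log-normal | Overall log-normal |
|---|---|---|---|---|
| One four-arm test | 4.9% | 9.8% | 3.3% | 8.2% |
| One t-test, IFN-α v no IFN-α | 5.0% | 9.8% | 3.6% | 8.5% |
| Three t-tests v the arm without add-ons | 12.6% | 17.0% | 8.2% | 12.8% |
| All six pairwise t-tests | 20.5% | 24.5% | 14.0% | 18.3% |

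Example for six pairs, normal data: 1 − 0.95 × (1 − 0.2045) = 24.4%, against 24.5% simulated.

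The table sets DTH at exactly 5%. A Kruskal-Wallis test with the usual chi-square cut-off has a true size of about 4.1% here. The log-normal figures then fall to 7.2% (one four-arm test), 11.9% (three) and 17.5% (six). This gives the ranges 7-10%, 12-17% and 17-25%.

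Correlation between DTH and ELISPOT lowers the figures a little. At 0.8, normal data, DTH at 5%, they are 8.1% (one four-arm test), 14.9% (three) and 21.7% (six).

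**Undefined ratio.** The article gives no ELISPOT counts, so Poisson counts are assumed. The probability of a net pre-vaccine count of zero or less, by stimulated and background means, is:

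- 2 and 2: 60%
- 5 and 5: 56%
- 5 and 3: 30%
- 5 and 2: 17%
- 10 and 3: 3%
- 20 and 5: 0.1%

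**Does the ratio inflate the error?** No. In every row of the table the skewed ratios give a lower a_E than normal data. The cost is power. For a three-fold difference with log-SD 1, the raw-ratio t-test has about 24% power at 6 v 6, against about 40% on the log scale. At 12 v 12 the figures are about 51% and 73%.

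**The case against.** The best defence is that this is a small proof-of-principle trial that does not claim strict error control. Much of it stands.

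- **No overall 5% is claimed.** A reader might infer that the protocol promises 5% and breaks the promise. It does not: 0.05 is a per-test level. The Secondary objectives section concedes a high risk of false positives, and Trial design and statistical considerations says the approach does not identify which regimens are significantly better. That concession, however, sits under the secondary objectives, quantifies nothing and leaves the success rule unchanged.
- **Regimen selection does not use these p-values.** A reader might infer that a worse regimen could be carried forward. The Sample size section selects by a gap of 2 patients in 6. Where the immunologic endpoint guides the choice instead, the protocol says the same selection method applies. The inflation therefore touches only the declaration that the objective is fulfilled.
- **A valid two-group reading exists.** The arms form a 2 × 2 layout, and a 12 v 12 contrast is possible. It would be wrong to say that the t-test can only mean six pairwise tests. But the neighbouring sections name that contrast and this one does not, so the text leaves it open.
- **The high figures depend on the reading.** The top of the range needs normal ratios and all six pairs. The protocol states neither, and normal ratios sit badly with the worry about extreme values.
- **Handling of zeros is ordinary SAP content.** That is fair for the missing rule. The choice of a raw ratio after subtraction, however, is fixed in the article itself.

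**Conclusion.** The point holds. The primary immunologic objective has two routes to success. The second opens only when DTH is not significant, carries no alpha adjustment, and uses a two-group test for four arms with no contrast named.

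The chance of a false declaration is about 7-10% with one ELISPOT test, 12-17% with three t-tests against the arm without add-ons, and 17-25% with six pairwise t-tests. These figures assume independent endpoints and DTH as one test at a nominal 0.05. No single range can be given as a bound, because the text does not fix the contrast. If the plural in the DTH wording meant several tests, the error would be higher still.

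The ratio is a separate weakness. A reader might infer that zero denominators help to drive up the error. They do not: skewed ratios make the t-test conservative, and the harm is lost power and lost patients. How often the ratio fails cannot be known from the document; the assumed counts span about 0.1% to 60%.

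**What to change.** 1. **Control the two routes.** Test DTH and ELISPOT together with Holm at an overall 0.05: the smaller p-value against 0.025 and, if that is met, the other against 0.05. The overall error is at most 5%; with independent endpoints it is 1 − 0.975 × 0.975 = 4.94%. Alternatively, let DTH alone fulfil the objective and call ELISPOT supportive, and amend the Immunologic objective section to match.
2. **Name one test per endpoint.** Replace the t-test in ELISPOT analysis by one prespecified four-arm test, for example Kruskal-Wallis or ANOVA on the log scale. Name a single four-arm test for DTH too, since Holm at 0.05 assumes one p-value per endpoint.
3. **Replace the ratio.** Analyse the post-minus-pre change in log((stimulated + 0.5)/(unstimulated + 0.5)), which is finite for every measured patient.

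**Cost.** Only wording changes, made before data are seen; no added patients, visits or assays. ELISPOT is tested at a slightly stricter level, or can no longer rescue a non-significant DTH result. A four-arm rank test may also have less power than one 12 v 12 contrast. For a three-fold difference with log-SD 1 at 0.05, Kruskal-Wallis has about 33% power if one arm differs and 46% if two do. The raw-ratio 12 v 12 t-test has about 51%. If a single factor contrast is what the sponsor wants, it should be named in advance as the one ELISPOT test and analysed on the log scale.

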### Assessment of the effects of preleukapheresis IFN-α on vaccine yield

The total number of vital ATL-loaded DC obtained from each leukapheresis will be measured by vital dye staining with trypan blue and microscopic counting after *in vitro* differentiation and maturation, according to the specific SOP currently adopted by the STC Lab. The value recorded will then be normalized to the volume of blood processed by leukapheresis (expressed in millilitres) to obtain the number of vital DC/ml of in processed blood. The distribution of vital DC number/ml of blood processed by leukapheresis observed in the different treatment arms (IFN-α *vs* no-IFN-α) will then be evaluated using the Student’s t-test and, if differences are found to be statistically significant, the specific primary objective will be considered fulfilled. Additional leukaphereses performed due to vaccine shortage will not be included in the analysis.

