#### Immunologic objectives

Secondary objectives also include the evaluation of the effects of preleukapheresis IFN-α on DC yield and potency, and of maturation-induced TEM8 expression on DC:

a) DC yield: the number of DC obtained per ml of blood processed by leukapheresis will be recorded at each leukapheresis and compared between the different treatment arms (IFN-α vs no-IFN-α);

b) DC potency: DC vaccine potency will be analyzed using an ELISPOT-based version of the COSTIM assay which will evaluate the co-stimulatory ability of dendritic cells;

c) TEM-8 upregulation observed upon DC maturation in non-immunoresponsive patients will be evaluated by qRT-PCR and the distribution of TEM-8 mRNA iDC: mDC ratio will be compared between the different treatment arms (IFN-α *vs* no-IFN-α). The percentage of patients in each treatment group reporting an adverse event (AE) up to 30 days after vaccination will be tabulated with 95% confidence intervals according to type of AE. The overall rate of grade 3–4 AEs will be calculated on the basis of treatment group. In addition, summary statistics of clinically significant laboratory abnormalities will be tabulated.

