### Assessment of the effects of preleukapheresis IFN-α on DC potency

#### Immunologic potency analysis

The co-stimulatory ability of the vaccine will be assessed with a modified version of the COSTIM assay [48] utilizing IFN-γ as a read-out system which has been used in our laboratory to assess the equivalence of freshly-made *vs* cryopreserved vaccine (data not shown). This GMP-validated method relies on the capacity of co-stimulatory signals provided by DC, *per se* unable to fully activate responder T cells, to trigger a proliferative response or cytokine secretion in allogeneic T cells stimulated with substimulating doses (0.005 mg/ml) of the anti-CD3 antibody OKT3. Briefly, 1×10^5^ reference T cells are co-cultured in quadruplicate with DC in IFN-γ ELISPOT plates for 24 hours at a T:DC ratio of 10:1, in the presence of 0.005 mg/ml OKT3. T cells cultured in the presence of 0.005 mg/ml OKT3 or DC are used as negative control. To ensure intra- and inter-assay reproducibility, reference T cells from at least 3 healthy donors are used for each determination. After a 24-hour incubation at 37°C in 5% CO2, plates are developed according to the manufacturer’s instructions and evaluated by a computer-assisted ELISPOT reader (Eli.Expert, A.EL.VIS GmbH). The distribution of SFC numbers across the different treatment arms (IFN-α *vs* no-IFN-α) will be evaluated according to the Student’s t-test and, if the differences are found to be statistically significant, the specific primary objective will be considered fulfilled. For this endpoint, only the first leukapheresis will be included in the analysis.

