#### Assessment of the effects of preleukapheresis IFN-α on TEM-8 expression

We demonstrated in previous works that patients who show upregulation of TEM-8 in DC after maturation (as assessed by flow cytometry and real-time PCR) do not develop anti-tumor immunity after DC vaccination. In order to assess this specific objective, total RNA will be extracted from immature and mature DC (5 × 10^6^ cells) and reverse transcribed to cDNA. Quantitative real-time PCR will be then performed using primer sets that cover all human TEM-8 splicing variants; appropriate housekeeping genes will also be amplified as normalization controls. The ratio between TEM-8 mRNA expression (normalized against housekeeping genes) in monocytes and in mDC will then be calculated. The distribution of the TEM-8 mRNA iDC:mDC ratio observed in the different treatment arms (IFN-α *vs* no-IFN-α) will be then evaluated using the Student’s t-test. If the differences are found to be statistically significant, the specific primary objective will be considered fulfilled.

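### Three secondary product assays (DC yield, DC potency, TEM-8) carry a decision rule that declares a primary objective fulfilled, in either direction

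*Protocol article*

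**What the plan says.** All places are in the protocol article.

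- **Primary objectives.** *Clinical objective* names irDCR. *Immunologic objective* says that immunologic efficacy "will be assessed by DTH development against KLH and tumor homogenate and also by IFN-γ-ELISPOT analysis of circulating effectors". No product assay appears in either.
- **Secondary objectives.** *Immunologic objectives* reads "Secondary objectives also include the evaluation of the effects of preleukapheresis IFN-α on DC yield and potency, and of maturation-induced TEM8 expression on DC", and its items (a) to (c) cover yield, potency and TEM-8.
- **Decision rules.** In *Assessment of the effects of preleukapheresis IFN-α on vaccine yield*: "if differences are found to be statistically significant, the specific primary objective will be considered fulfilled". In *Immunologic potency analysis*: "if the differences are found to be statistically significant, the specific primary objective will be considered fulfilled". In *Assessment of the effects of preleukapheresis IFN-α on TEM-8 expression*: "If the differences are found to be statistically significant, the specific primary objective will be considered fulfilled". Each rule follows a Student's t-test of IFN-α against no IFN-α.
- **The same rule for measures that are primary.** *Immunologic efficacy* applies it to DTH. *ELISPOT analysis* applies it with the only stated level: "If differences are found to be statistically significant (significance level 0.05), the specific primary objective will be considered fulfilled".
- **TEM-8 variable.** RNA is taken from immature and mature DC. The ratio of expression "in monocytes and in mDC will then be calculated". The quantity then tested is the iDC:mDC ratio.

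**The concern.** The list of objectives and the decision rules disagree on what counts as primary. Anyone applying the rules as written would credit a primary objective on the strength of a manufacturing or laboratory measure. More DC per millilitre of blood could be published as a met primary objective in a trial that changed neither immune response nor disease control.

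Two further defects sit in the same three sections. The rules name no direction, so a significant disadvantage of IFN-α meets them as well as an advantage does. And the TEM-8 section names two different denominations for one ratio: monocytes in the sentence that defines it, iDC in the sentence that analyses it.

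**Working it through.** **1. Label against rule**

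| Measure | Status in the objectives | What a significant test fulfils |
|---|---|---|
| DTH | primary | a primary objective |
| ELISPOT | primary | a primary objective |
| DC yield | secondary | a primary objective |
| DC potency | secondary | a primary objective |
| TEM-8 ratio | secondary | a primary objective |

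The first two rows agree and the last three do not. Nothing in the article reclassifies the three assays.

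**2. Direction.** *Potential effects of Interferon-α (IFN-α) on circulating precursors of DC* expects more immunogenic DC, better leukapheresis yields and, more tentatively, suppression of TEM-8 upregulation. The three rules require only that groups differ. Sidedness is not stated.

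**3. TEM-8 ratio.** The RNA sources are iDC and mDC, *Immunologic objectives* item (c) gives iDC:mDC, and so does the analysis sentence. Only the sentence in between says monocytes, and no extraction of monocyte RNA is described.

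**4. Size.** The article gives no overall error rate for these tests. Its own error figure is the 10% probability of selecting an inferior arm (*Sample size*: 6 per arm, gap of 2, difference of 15%). Exact binomial enumeration with one arm better by 0.15 puts the wrong-selection probability at a maximum of 8.6% with four arms and 8.1% with two, so that figure reproduces. It concerns selection of an arm and does not cover the t-tests.

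Inputs for the t-tests: level 0.05 each (stated for ELISPOT, assumed for the rest), two-sided, independent, no true effect.

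- Three mislabelled tests: 1 − 0.95³ = 1 − 0.8574 = 0.143. Whatever the dependence, the ceiling is 3 × 0.05 = 0.15.
- The same three, counting only false results in the favourable direction (0.025 each): 1 − 0.975³ = 1 − 0.9269 = 0.073.
- DTH, then ELISPOT only if DTH fails: 0.05 + 0.95 × 0.05 = 0.0975.
- All five: 1 − 0.95⁵ = 1 − 0.7738 = 0.226, with a ceiling of 5 × 0.05 = 0.25.

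Independence is doubtful because the measures come from the same patients. A null simulation of all five tests used four arms of 6: a Kruskal–Wallis test for DTH, one global ELISPOT test only if DTH fails, and three t-tests of 12 against 12. At least one success occurred in 21.6%, 20.9%, 19.1% and 15.1% of trials at between-endpoint correlations of 0, 0.3, 0.5 and 0.8. If ELISPOT were instead tested by all six pairwise t-tests, the range would be about 27% to 34%.

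**The case against.** The strongest defence is the word *specific*. Each rule can be read as settling its own objective, and the article nowhere says that one significant test makes the trial positive. That reading is fair, and it removes any claim about success of the trial as a whole. It does not rescue the label: the objective that each assay settles is listed as secondary, so calling it primary is wrong on either reading.

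Second, the assays do not decide the outcome of the trial. *Trial design and statistical considerations* and *Sample size* choose a regimen on irDCR or on immune response. This stands. The harm is confined to what may be reported as primary.

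Third, multiplicity control is commonly left to an analysis plan that is not shown, and the section on secondary clinical objectives concedes exploratory intent and a high risk of false positives. The absence of an adjustment is therefore not the finding. The concession still gives no ground for presenting secondary assays as primary.

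Fourth, the TEM-8 discrepancy is one word, and the intended variable can be recovered from the text around it. That is correct, and the slip is minor. On direction, the rationale makes the intent clear, but the rules as worded do not carry it.

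**Conclusion.** The contradiction is certain, because it stands in the text. Three objectives listed as secondary have rules that declare a primary objective fulfilled, without regard to direction. It affects the claims that the trial may make, not the arm that it selects.

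The size attributable to it is a 14.3% chance of at least one false declaration from the three assays. This assumes 0.05 per test, independence and no true effect.

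A reader might infer that the plan offers five uncorrected routes to a positive trial, at 22.6%. The documents do not support this as a flat statement. DTH and ELISPOT are legitimately primary, the rule is tied to each specific objective, 0.05 is stated only for ELISPOT, and no text makes a single success sufficient for the trial. The 22.6% applies only if any one success is read as primary success. DTH and ELISPOT alone would still give about 9.75% after the labels are corrected.

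**What to change.** In the yield, potency and TEM-8 sections, replace *specific primary objective* with *specific secondary objective*. In each, count it as fulfilled only if the significant difference lies in the hypothesised direction: higher yield, higher potency, less TEM-8 upregulation under IFN-α. Since upregulation on maturation lowers an iDC:mDC ratio, the favourable direction for TEM-8 is a higher ratio, and the text should say so.

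In the TEM-8 section, replace *monocytes* with *iDC* in the sentence that defines the ratio, so that it matches the RNA sources, the analysis sentence and the secondary objective.

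The cost is wording only: no added patients, samples or assays. The sponsor gives up the option of presenting a product-assay result as a fulfilled primary objective. Analysis of the ratio on a log scale and reporting of differences with confidence intervals would be sensible, but they are choices for the analysis plan and the correction does not depend on them.
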